#### Blinding (Masking)

The assessments of outcome variables will be conducted by RAs who are blinded to the treatment allocation. Owing to the nature of the intervention, neither the participants nor the therapist can be blinded to the treatment allocation, but they are strongly encouraged not to disclose the participants’ allocation status during the assessments. An RA will enter the data into a computer on separate datasheets, and a senior RA will conduct the data analysis under the supervision of the principal investigator (PI; [name]).

### Data Collection Methods

#### Research Questions 1-2 (Participants: Older Adults)

A therapist on the Short-Term Assessment, Rehabilitation, and Treatment Psychiatry Day Hospital program at Glenrose Rehabilitation Hospital with an RA, that is, RA 1, will administer the intervention (5 video screenings). The control group will receive standard care at the Short-Term Assessment, Rehabilitation, and Treatment Psychiatry Day Hospital program Glenrose Rehabilitation Hospital. The PANAS scale will be administered after each session along with the 3Scape videos to the intervention group participants (10 minutes). The GAD-7, HoNOS, and OPQoL-Brief will be administered to all participants at the beginning and end of the Short-Term Assessment, Rehabilitation, and Treatment program, as this is part of the standard care. In addition, we will administer the same measures (ie, GAD-7, HoNOS, and OPQoL-Brief) to the participants on both arms before and after each group therapy is conducted (ie, 6 weeks apart). The administration of these measures will take approximately 30 minutes. RA 2, who will be blinded to the group allocation, will administer these measures. The participants will be asked not to inform the evaluators about the kind of intervention they had received. The sessions will be conducted in a quiet room at the Courage Center.

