### Outcome Variables

#### Research Questions 1-2 (Primary Outcome Variables)

Older adults’ depressive and anxiety symptoms, mood, overall quality of life, and engagement are the primary outcome variables for these research questions. Older adults’ depressive and anxiety symptoms will be assessed using the Generalized Anxiety Disorder-7 item (GAD-7) scale patient self-report tool [21] and the Health of the Nation Outcome Scale (HoNOS; a clinician rating tool) symptoms [22], older adults’ mood will be measured using PANAS (20-item self-report questionnaire) [23], and older adults’ overall quality of life will be measured using Older People’s Quality of Life-Brief (OPQoL-Brief) questionnaire scale-13 items self-reported tool [24].

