#### Research Questions 1-2 (Secondary Outcome Variables)

Engagement while watching the 3Scape videos will be measured using an engagement scale developed by team members in a previous study [25]. This is an 8-point Likert scale that has been shown to be understood by older adults, even those with mild cognitive impairments.

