#### Control Group (Participants: Older Adults)

Research question 1-2 (Primary outcome variables): at the enrollment of the program (week 0 [T_0_], called the pretest program enrollment), week 12 (T_1_), and at the posttest when the participants finish the program and watch the videos (week 18 [T_8_]).

For the therapists involved in the intervention group, the measurements will be taken as follows: research questions 4 and 5 (participants, therapists): week 12 [T_1_].

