### Data Analyses

#### Research Questions 1, 2, and 3

The analyses will be conducted in SPSS using intention-to-treat principles. Descriptive statistics will be used to characterize the groups during the pretest. Owing to the small sample size, comparisons of the GAD-7, HoNOS, OPQoL-Brief, and PANAS scores within the groups will be performed using a Wilcoxon signed-rank test (*P*≤.05), and comparisons between the groups will be calculated using the Mann–Whitney *U* test (*P*≤.05). The GAD-7, HoNOS, OPQoL-Brief, and PANAS scores will be used to analyze the clinical significance, established as a change of 2 or more units [30]. Participants’ engagement will be analyzed using descriptive statistics.

#### Research Question 4

The audiotapes will be transcribed and content analysis will be performed. The content analysis will be data driven. Data codes will be inductively generated using the data collected. Through the coding, a small number of themes or categories will be generated. The analyses will be performed by an RA, and a consensus in the interpretations will be achieved through a discussion among the research team members. The validity of the interpretations will be discussed with and agreed upon by every member of the research team. NVivo 10 software will be used to conduct data analysis.

#### Research Question 5

Descriptive statistics will be used to characterize the groups at pretest and posttest. Owing to the small sample size, comparisons of the MBI-HSS MP scores within the groups will be performed using a Wilcoxon signed-rank test (*P*≤.05), and comparisons between the groups will be calculated using a Mann–Whitney *U* test (*P*≤.05).

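### The protocol contradicts itself on whether controls receive PANAS, the instrument for the primary outcome mood, so the planned mood tests depend on which section staff follow

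*Protocol article*

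**What the plan says.** **Status of mood.** Outcome Variables states: "Older adults’ depressive and anxiety symptoms, mood, overall quality of life, and engagement are the primary outcome variables for these research questions". It names the instrument: "older adults’ mood will be measured using PANAS (20-item self-report questionnaire".

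**Collection.** Data Collection Methods, Research Questions 1-2, says: "The PANAS scale will be administered after each session along with the 3Scape videos to the intervention group participants (10 minutes". For the other scales it says: "we will administer the same measures (ie, GAD-7, HoNOS, and OPQoL-Brief) to the participants on both arms before and after each group therapy is conducted". The preceding sentence, on the start and end of the program, names the same three scales for all participants. PANAS is in neither list. The Experimental (Intervention) Group section also places PANAS inside the video session, after the discussion.

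**Schedule.** Table 1 marks PANAS for both arms at T0, T1 and T8, and for the intervention arm alone at the columns between. The Participant Timeline puts the primary outcomes in both arms at weeks 0, 12 and 18.

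**Analysis.** Data Analyses says: "comparisons of the GAD-7, HoNOS, OPQoL-Brief, and PANAS scores within the groups will be performed using a Wilcoxon signed-rank test". Between-group comparisons use the Mann-Whitney test.

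**Related wording.** The secondary-outcome paragraph says: "Engagement while watching the 3Scape videos will be measured using an engagement scale". The control-arm schedule places the last assessment "at the posttest when the participants finish the program and watch the videos".

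**The concern.** Research question 2 asks whether mood differs from that of clients receiving standard care. Answering it needs PANAS scores from controls, and a change analysis needs scores from before the first video. The section that tells staff what to hand out, to whom and when provides neither. Nothing in the article says which section prevails.

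A missed week-0 or week-12 score cannot be collected later, so the error would surface only at analysis. The pilot is also meant to supply estimates for a definitive trial, and for mood it would then have no between-arm estimate to offer.

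**Working it through.** No published figure is at issue, so the check sets the sections side by side and counts scores. The denominator comes from Sample Size: 24 / (1 − 0.20) = 30, or 15 per arm, as the protocol states. Counts assume full attendance and no dropout.

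**Step 1: what each section gives.**

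| Section | Control PANAS | Intervention PANAS |
|---|---|---|
| Data Collection, Research Questions 1-2 | none listed | after each of 5 sessions |
| Experimental (Intervention) Group | not addressed | within the video session |
| Table 1 | T0, T1, T8 | T0, T1, T8 and 5 columns between (T2, T3, T5, T6, T7) |
| Participant Timeline (primary outcomes) | weeks 0, 12, 18 | weeks 0, 12, 18 |
| Data Analyses | needed for both tests | needed for both tests |

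**Step 2: scores available.**

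- Data Collection governs: controls 0 × 15 = 0. Intervention 5 × 15 = 75, all post-session, with none before the first video.
- Table 1 governs: controls 3 × 15 = 45. Intervention 8 × 15 = 120, of which 3 × 15 = 45 fall at the shared visits and 75 are post-session.

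**Step 3: what can be analysed.**

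- *Mann-Whitney between arms.* Under Data Collection there is no control sample, so no test. Under Table 1 there are up to 15 against 15 at T8, or 12 against 12 after the planned 20% dropout.
- *Wilcoxon within arms.* Under Data Collection controls have no scores. The intervention arm could compare its first session with its last, but that is not a change from before treatment. Under Table 1 both arms have T1 and T8.
- *Change of 2 or more units.* This criterion needs the same baseline and fails or stands with the Wilcoxon test.

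**Step 4: who administers it.** The Blinding section says outcomes are assessed by blinded research assistants. RA 2, who is blinded, gives GAD-7, HoNOS and OPQoL-Brief. The post-session PANAS is given by research staff at the screening, where allocation is evident.

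**Step 5: can Table 1 be taken to prevail?** Not automatically. It marks engagement at T0 and T1, before any video is shown. It also marks GAD-7, HoNOS and OPQoL-Brief in the intervention arm at all 8 columns, where the Timeline gives three time points. It has its own conflicts with the text.

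**Step 6: related wording.** Engagement is primary in one paragraph, secondary in the next and in Table 1, marked for the intervention arm only, and analysed descriptively. The control schedule's reference to watching the videos conflicts with the Control Group and Data Collection sections, where controls receive standard care.

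**The case against.** The strongest reply is that Data Collection never says PANAS is given only to the intervention arm. It can be read as describing the extra post-session assessments while omitting the shared ones. Table 1 fits this: its five intervention-only columns match the five screenings, and it marks controls at T0, T1 and T8. The Timeline agrees, and Data Analyses presupposes the data. This stands as a limit on the finding: the protocol shows a conflict, not a settled decision to leave controls unmeasured. It does not remove the conflict, because the both-arm set is spelled out twice without PANAS.

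A reader might infer that the trial has no randomised mood comparison, or that any PANAS contrast would capture only the immediate after-video state. The documents do not support that. The Timeline puts T1 at week 12 before any video, the post-video measurements in weeks 13-17, and T8 at week 18. A T8 comparison therefore follows the screening weeks. The after-video problem arises only if session scores stand in for T8, which no section proposes.

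A reader might also infer that engagement breaks a planned test because controls cannot have it. No between-arm test of engagement is planned, so this is a labelling fault. Nor does the control schedule show that controls are exposed to the videos: the sentence has the same wording as the intervention-arm schedule and looks carried over.

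Two further points moderate the weight. The Discussion names feasibility as the primary objective, and the other three tested scales are clearly collected in both arms. PANAS is also self-reported by unblinded participants, so a blinded administrator protects it only in part.

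**Conclusion.** The protocol is wrong as written on who receives PANAS. The size depends on which section is followed. Under Data Collection, one of the four tested scales has 0 of 15 control scores and no pre-video scores in either arm, and neither planned test of mood can be run as a comparison between arms or from before to after the videos. Under Table 1 and the Timeline nothing is lost. The article does not say which applies, and a full protocol not seen here may settle it. The conclusion is therefore an unresolved contradiction over a primary outcome, to be settled before further data are collected, and not a finding that control mood data will be absent. The engagement label and the control-schedule wording are minor.

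**What to change.** In Data Collection Methods, Research Questions 1-2:

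- Add PANAS to the measures that RA 2 gives to both arms at T0, T1 and T8, under the same conditions in each arm.
- State that these scores feed the Wilcoxon and Mann-Whitney tests in Data Analyses.
- State that the post-session PANAS is descriptive intervention-arm data and does not replace the T8 score.

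Minor corrections: remove engagement from the primary list in Outcome Variables, and reconcile the phrase about watching the videos in the control schedule with the Control Group and Data Collection sections.

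The cost is protocol wording plus about 10 minutes of questionnaire time (the protocol's own figure for PANAS) at each of three visits that both arms already attend, or 3 × 10 = 30 minutes per participant. Table 1 already schedules these assessments. The study was launched and then put on hold, so if anyone was enrolled before the pause, check whether their shared-visit PANAS was taken and report any gap.

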### Participant Timeline

#### Overview

This feasibility trial consisted of a 6-week intervention treatment phase; this study does not have a follow-up phase. The total trial data collection period will be 8 months. As shown in Table 1, Figure 2, and Figure 3, the measurements will be taken as follows.

**Table 1 table1:** Key variables and measurements.

Variables			Participants		Measurement		T_0_		T_1_		T_2_		T_3_		T_5_		T_6_		T_7_		T_8_

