**Primary outcome**																					
	GAD-7^a^	Older adults		GAD-7 scale		✓^b,c,d^		✓^c,d^		✓^d^		✓^d^		✓^d^		✓^d^		✓^d^		✓^c,d^	
	HoNOS^e^	Older adults		HoNOS, a clinician rating tool		✓^c,d^		✓^c,d^		✓^d^		✓^d^		✓^d^		✓^d^		✓^d^		✓^c,d^	
	OPQoL-Brief^f^	Older adults		OPQoL-Brief scale		✓^c,d^		✓^c,d^		✓^d^		✓^d^		✓^d^		✓^d^		✓^d^		✓^c,d^	
	PANAS^g^	Older adults		PANAS		✓^c,d^		✓^c,d^		✓^d^		✓^d^		✓^d^		✓^d^		✓^d^		✓^c,d^	

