**Covariates**																					
	Demographics	Older adults and therapists		Self-report assessment questionnaire		✓^c,d^															

^a^GAD-7: Generalized Anxiety Disorder-7.

^b^Outcome present.

^c^Control groups.

^d^Intervention groups.

^e^HoNOS: Health of the Nation Outcome Scale.

^f^OPQoL-Brief: Older People’s Quality of Life-Brief.

^g^PANAS: Positive and Negative Affect Schedule.

^h^MBI-HSS MP: Maslach Burnout Inventory-Human Services Survey for Medical Personnel.

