#### Intervention Group (Participants: Older Adults)

Research questions 1-2 (primary outcome variables): at the enrollment of the program (week 0 [T_0_], called the pretest program enrollment), the pretest before starting showing the videos (week 12 [T_1_]), and at the posttest when the participants finish the program and watch the videos (week 18 [T_8_]).

Research questions 1-2 (secondary outcome variables): after watching each video, that is, weeks 13-17 (T_1-7_).Research question 3 (participants, older adults): after watching every video (week 18 [T_8_]).

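### Table 1 schedules GAD-7, HoNOS and OPQoL-Brief eight times in the intervention arm and three times in controls, while the text gives both arms the same schedule

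*Protocol article*

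**What the plan says.** The Participant Timeline overview makes the table operative: "As shown in Table 1, Figure 2, and Figure 3, the measurements will be taken as follows". Table 1 uses one footnote letter for controls and another for the intervention arm. In the GAD-7, HoNOS and OPQoL-Brief rows the intervention letter stands in all eight columns. The control letter stands only at T0, T1 and T8. The HoNOS row is labelled "HoNOS, a clinician rating tool".

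The text describes something else:

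- **Participant Timeline, Intervention Group.** Primary outcomes are taken at weeks 0, 12 and 18. Only the secondary outcome, engagement, follows each video: "Research questions 1-2 (secondary outcome variables): after watching each video, that is, weeks 13-17".
- **Participant Timeline, Control Group.** The same three points, with the later two given as "week 12 (T_1_), and at the posttest when the participants finish the program" (week 18).
- **Data Collection Methods, Research Questions 1-2.** The three scales go to everyone at the start and end of the program. In addition, "we will administer the same measures (ie, GAD-7, HoNOS, and OPQoL-Brief) to the participants on both arms before and after each group therapy", six weeks apart. Only PANAS is tied to each video session.
- **Experimental (Intervention) Group.** The one-hour session contains PANAS and a postscreening survey and no other questionnaire.

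On masking, the Blinding section states: "The assessments of outcome variables will be conducted by RAs who are blinded to the treatment allocation". For these three scales Data Collection Methods is specific: "RA 2, who will be blinded to the group allocation, will administer these measures".

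**The concern.** Staff working from Table 1 and staff working from the text would run different trials. Two things are at stake in the week-18 comparison between arms.

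- **Assessor blinding.** RA 2 is the only assessor named for these scales. Under Table 1, everyone RA 2 saw between weeks 12 and 18 would be an intervention participant, so the appointment itself would disclose the arm before the posttest. The exposure is greatest for HoNOS, where the rater supplies the score. GAD-7 and OPQoL-Brief are self-reports by patients who know their arm. If the assistant present at the screenings gave the scales instead, that person would be unblinded and the Blinding section would not be met.
- **Comparability.** Five extra rounds of testing and contact in one arm would be mixed with the effect of the videos.

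Research question 1 asks whether this protocol is feasible, so the assessment load is itself something the trial should fix clearly.

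**Working it through.** **Inputs.** Tick pattern: Table 1 and its footnotes. Time per round of the three scales: about 30 minutes (Data Collection Methods). Participants: 15 per arm (Sample Size). The stated sample size reproduces (12 per arm for an effect size of 1.20, then 24 / 0.8 = 30) and has no bearing on this point beyond supplying the 15.

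**Step 1: count the ticks.** The pattern is the same for GAD-7, HoNOS and OPQoL-Brief.

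| | T0 | T1 | T2 | T3 | T5 | T6 | T7 | T8 | Total |
|---|---|---|---|---|---|---|---|---|---|
| Table 1, intervention | x | x | x | x | x | x | x | x | 8 |
| Table 1, control | x | x | | | | | | x | 3 |
| Timeline text, intervention | x | x | | | | | | x | 3 |
| Timeline text, control | x | x | | | | | | x | 3 |

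Extra rounds in one arm: 8 − 3 = 5. These five columns lie between week 12 and week 18 and match in number the five videos in weeks 13 to 17.

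**Step 2: size if Table 1 governs.**

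- Administrations per scale: 15 × 8 = 120 against 15 × 3 = 45.
- Visits that would reveal the arm: 15 × 5 = 75.
- Extra administrations: 5 rounds × 3 scales × 15 participants = 225.
- Testing time per participant: 8 × 30 = 240 minutes against 3 × 30 = 90 minutes, a difference of 150 minutes.
- For the arm: 150 × 15 / 60 = 37.5 hours.

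The video hour is already full: 20 (video) + 20 (discussion) + 20 (questionnaires) = 60 minutes. A round placed inside it would make 90 minutes, but nothing in the article says it would be placed there.

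**Step 3: size if the text governs.** The arms have equal schedules, so there are no one-arm rounds for these three scales. Data Collection Methods could be read as more than three occasions, but equally in both arms, so its conflict with Table 1 remains.

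**Step 4: check PANAS separately.** Outcome Variables lists PANAS as primary. Weekly PANAS in the intervention arm agrees with Table 1, the session description and Data Collection Methods. It disagrees with the Intervention Group timeline, which places primary outcomes only at weeks 0, 12 and 18.

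**The case against.** The best reply is that Table 1 is a drafting slip. The session description, both timeline paragraphs and Data Collection Methods all keep the three scales out of the weekly sessions. Table 1 is careless elsewhere: it has no T4 column, and it ticks engagement with the videos at T0 and T1, before any video is shown. The overview also points to Figures 2 and 3, which were not available here and might settle the matter. This stands as evidence of intent: the text is what was meant. It does not remove the conflict, because the overview sends the reader to the table.

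A reader might infer that assessor blinding is possible only under the text. That goes too far. A separate assessor at T2 to T7 would leave RA 2 blinded for week 18, although none is named. Nor does the text schedule secure blinding alone. The Implementation paragraph under Allocation gives the code assigned at allocation to the assessing assistants, without saying whether it identifies the arm. The research team present at the screenings gives PANAS, and RA 2 also conducts the surveys for research question 4.

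A reader might also take the Discussion's four measurement occasions as support for Table 1. That does not follow. Data Collection Methods can itself be read as four (program start, program end, before and after a group therapy), and six-weekly testing over 18 weeks also gives four (weeks 0, 6, 12 and 18). The Control Group description gives a 20-week stay, so program end need not be week 18. The same Discussion paragraph cites a 10-week period that fits no schedule in the article and restart dates a year earlier than the Results section, so it is weak evidence either way.

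**Conclusion.** The contradiction is exact: 8 against 3 assessments in Table 1 and equal schedules in the text, for three primary scales. It is more than clerical. Following the table with RA 2 as assessor would disclose the arm before the posttest and put five one-arm test rounds ahead of the between-arm comparison.

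The 75 visits, 225 administrations and 37.5 hours assume that Table 1 governs, that all 15 intervention participants attend every round, and that a round takes 30 minutes. Under the text all three are zero. The effect on scores cannot be computed from the article. The blinding consequence also assumes that no second assessor is used, and it bears mainly on HoNOS.

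The documents do not show that blinding has failed, nor that the intended schedule is unknowable. The text schedule is needed for RA 2's blinding as the trial is staffed on paper, but it is not sufficient for it.

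**What to change.** - Delete the T2, T3, T5, T6 and T7 ticks from the GAD-7, HoNOS and OPQoL-Brief rows of Table 1, so that it follows the text.
- Keep the weekly intervention-arm PANAS as a within-session measure, say so in the Intervention Group timeline, and limit the between-arm PANAS comparison to T0, T1 and T8. One-arm repeated testing remains for PANAS and should be acknowledged when that comparison is reported.
- Align the four occasions and the 10 weeks in the Discussion with the schedule finally chosen. Do not simply rewrite them as three time points until the number of occasions in Data Collection Methods is settled.
- If repeated measurement of the three scales is wanted, schedule it in the same weeks in both arms.

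**Cost.** Fifteen ticks (5 columns × 3 rows), one timeline amendment and one Discussion correction, with no added visits or participants. What is given up is a weekly course of three scales that has no control counterpart in Table 1 and that no analysis in Data Analyses specifically requires. Repeated measurement in both arms would instead add the same five rounds in controls: 5 × 30 × 15 / 60 = 37.5 hours.
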